## Abstract

**Background/Objectives:** Children with Autism Spectrum Disorder (ASD) often display heightened sensitivity to simple auditory stimuli, but have difficulty discriminating and integrating multiple phonological features (segmental: consonants and vowels; suprasegmental: lexical tones) at the syllable level, which negatively impacts their communication. This study aims to investigate the neural basis of segmental, suprasegmental and combinatorial speech processing challenges in Mandarin-speaking children with ASD compared with typically developing (TD) peers. **Methods:** Thirty children with ASD and thirty TD peers will complete a multi-feature oddball paradigm to elicit auditory ERP during passive listening. Stimuli include syllables with single (e.g., vowel only), dual (e.g., vowel + tone), and triple (consonant + vowel + tone) phonological deviations. Neural responses will be analyzed using temporal principal component analysis (t-PCA) to isolate overlapping ERP components (early/late MMN), and representational similarity analysis (RSA) to assess group differences in neural representational structure across feature conditions. **Expected Outcomes:** We adopt a dual-framework approach to hypothesis generation. First, from a theory-driven perspective, we integrate three complementary models, Enhanced Perceptual Functioning (EPF), Weak Central Coherence (WCC), and the Neural Complexity Hypothesis (NCH), to account for auditory processing in ASD. Specifically, we hypothesize that ASD children will show enhanced or intact neural discriminatory responses to isolated segmental deviations (e.g., vowel), but attenuated or delayed responses to suprasegmental (e.g., tone) and multi-feature deviants, with the most severe disruptions occurring in complex, multi-feature conditions. Second, from an empirically grounded, data-driven perspective, we derive our central hypothesis directly from the mismatch negativity (MMN) literature, which suggests reduced MMN amplitudes (with the exception of vowel deviants) and prolonged latencies accompanied by a diminished left-hemisphere advantage across all speech feature types in ASD, with the most pronounced effects in complex, multi-feature conditions. **Significance:** By testing alternative hypotheses and predictions, this exploratory study will clarify the extent to which speech processing differences in ASD reflect cognitive biases (local vs. global, per EPF/WCC/NCH) versus speech-specific neurophysiological disruptions. Findings will advance our understanding of the sensory and integrative mechanisms underlying communication difficulties in ASD, particularly in tonal language contexts, and may inform the development of linguistically tailored interventions.

## 1. Introduction

Autism Spectrum Disorder (ASD) is a neurodevelopmental condition characterized by differences in social interaction, speech communication, and other behaviors, including sensory processing difficulties [1]. Language difficulties are common in ASD but vary widely, influenced by factors such as cognitive abilities, symptom severity, and co-occurring conditions [2]. This heterogeneity underscores the importance of investigating both basic auditory encoding and higher-order integrative mechanisms to better understand the diverse language profiles observed in ASD.

Prior research has linked language challenges in ASD to atypical discrimination of both nonspeech and speech sounds [3,4,5]. Despite growing interest in auditory processing in ASD, most studies have focused on a narrow range of auditory contrasts, often isolating segmental or suprasegmental features without investigating how multiple features are processed together [6]. This limits our understanding of how children with ASD perceive complex, ecologically valid speech signals. To address this, we examine Mandarin Chinese, a tonal language in which lexical meaning is determined by contrasts in consonants (C), vowels (V), and tones (T). This provides a rich, structured context to explore how children with ASD discriminate and integrate multiple phonological features, both in isolation (C, V, T) and in combination (e.g., C + V, V + T, C + T, C + V + T), as they naturally occur in Mandarin words.

However, no single existing theoretical framework directly predicts the exact pattern of differences between children with ASD and typically developing (TD) peers across the seven types of speech contrasts examined in this exploratory study. To address this, we review experimental findings and protocols on the processing of lexical tones, vowels, and consonants as well as complementary theoretical perspectives from existing literature to inform our experimental design. We will also develop theory-driven and data-driven hypotheses and predictions regarding how ASD may influence the neural processing of single- and multi- feature speech contrasts, at both local (segmental) and global (beyond segmental) levels.

### 1.1. Atypical Acoustic Speech Feature Processing in ASD

Speech perception involves the multi-dimensional encoding of acoustic features such as fundamental frequency (F0), voice onset time, formant transition, and formant structure [7,8,9]. To assess how the brain automatically discriminates these acoustic variations, researchers commonly use the mismatch negativity (MMN), an event-related potential (ERP) component that reflects pre-attentive auditory discrimination [10]. MMN is particularly valuable for studying the neural mechanisms underlying early auditory perception. Its key advantage lies in being a “pre-attentive” ERP component, meaning it can be elicited while participants are passively listening, not actively attending to the stimuli. This makes it particularly valuable for research with populations who may have difficulty following complex instructions or sustaining attention, such as infants, young children, and individuals with neurodevelopmental conditions like ASD. Importantly, MMN responses for speech sounds in early childhood have been found to be predictive of subsequent language and reading skills, indicating their relevance for early screening and intervention planning in children at risk for language impairments [11,12].

#### 1.1.1. Lexical Tone Processing

In tonal languages like Mandarin, pitch contours, which are conveyed through F0 variations at the syllable level, create lexical contrasts (e.g., “妈” [mā] with a flat tone means “mother,” while “骂” [mà] with a falling tone means “scold”). In contrast, non-tonal languages (e.g., English) use pitch for prosodic functions like intonation and emphasis [13,14,15]. This distinction is critical for understanding auditory processing in ASD, where research reveals a dissociation between non-speech and speech-related pitch processing. While individuals with ASD often exhibit intact or enhanced sensitivity to simple, non-speech pitch changes (e.g., demonstrating faster reaction times and stronger MMN responses to frequency deviants [16]), they struggle to integrate pitch information into more complex contexts [17,18]. For instance, despite heightened pitch discrimination, individuals with ASD struggle with auditory stream segregation [19], suggesting a bias toward local pitch features at the expense of integrating these features into different voice streams.

This pattern is particularly evident in tonal language studies. Children with ASD show reduced MMN amplitudes in response to Mandarin and Cantonese tone contrasts, even though they exhibit enhanced MMN responses to non-speech pitch deviations [20,21]. They also do not show the typical enhancement of MMN for between-category tone contrasts compared to within-category acoustic differences, indicating difficulties with categorical perception of lexical tones [22]. These findings suggest that while basic pitch detection may be preserved or heightened in ASD, the integration of dynamic F0 contours with phonological and linguistic context is problematic [20,23,24,25]. Thus, the core challenge lies not in detecting pitch changes, but in assigning them linguistic meaning within a speech signal.

#### 1.1.2. Consonant Processing

Unlike suprasegmental features such as lexical tone, consonants are primarily identified by transient acoustic cues such as voice onset time (VOT), formant transitions, burst amplitude, and spectral properties [26]. These rapid, dynamic changes require precise auditory temporal resolution for accurate perception. Kuhl et al. (2005) found that typically developing (TD) children elicited a clear MMN response to the /ba/ vs. /wa/ contrast, whereas children with ASD did not, indicating reduced sensitivity to consonantal contrasts in ASD [27]. This finding has been interpreted as a deficit in early phonetic discrimination. Additionally, children with ASD demonstrate less categorical perception of VOT contrasts for stop consonants, indicating atypical encoding of phonemic boundaries [28]. These perceptual difficulties likely stem from challenges in rapid acoustic discrimination, which relies on fine-grained auditory timing [29,30]. Children with ASD show longer latencies in auditory evoked responses, reduced neural synchrony and lower MMNs [31,32,33]. Such disruptions in neural timing may affect the brain’s ability to parse brief, rapidly occurring cues such as formant transitions or burst timing that are critical for consonant identification.

However, an important caveat arises from a follow-up analysis in which the ASD group was subdivided based on auditory preference [27]. Children with ASD who preferred non-speech stimuli still failed to elicit an MMN, consistent with the initial finding. In contrast, those who preferred motherese (infant-directed speech) showed MMN amplitudes comparable to TD controls. This suggests that individual differences in sensory preference and attentional engagement may modulate neural speech discrimination in ASD.

#### 1.1.3. Vowel Processing

Vowels are primarily distinguished by their first and second formants (F1 and F2). Research shows that children with ASD demonstrate significant differences in vowel processing across multiple levels, ranging from early sensory encoding to higher-order attentional mechanisms [34]. There is evidence that intact MMN responses to vowel contrasts can be found in some individuals with ASD, especially in high-functioning cohorts without language impairment. However, differences in MMN latency, amplitude, or hemispheric lateralization are also reported, particularly in ASD subgroups with more pronounced language difficulties [3,35]. These inconsistencies may stem from variations in the population studied (e.g., language ability), stimulus design, and analysis methods.

Compared to their TD peers, children with ASD show prolonged MMN latencies in response to vowel deviants, indicating delayed neural encoding of relatively steady formant structure [36,37]. Attentional mechanisms are also affected. The P3a component, which follows MMN and reflects automatic attention shift [38,39], is reduced in response to vowel (but not non-speech) deviants in ASD [32,40,41]. This pattern points to a speech-specific problem in attentional engagement, suggesting that while basic acoustic change detection may be preserved, the subsequent allocation of attention to speech-relevant changes is diminished.

### 1.2. Integration Differences in ASD

#### 1.2.1. Cross-Feature Integration in Speech Perception

In natural speech, phonological features do not operate in isolation. Instead, consonants, vowels, and tones interact dynamically to convey meaning [42,43,44]. For example, tone realization in Mandarin depends on concurrent changes in fundamental frequency (F0) and first formant (F1), while stop consonant identification relies on formant transitions into following vowels [45]. This multi-dimensional, temporally overlapping structure of speech requires the auditory system to rapidly integrate acoustic cues across time and frequency domains.

However, individuals with ASD often exhibit disruptions in this integrative process, despite intact or even enhanced sensitivity to isolated acoustic features [46]. A key example comes from Lepistö et al. (2008), who found that while children with ASD showed enhanced neural sensitivity to pitch or phoneme changes presented in isolation, this advantage disappeared when pitch varied within a phoneme, suggesting a failure to extract invariant speech patterns from variable acoustic input [47]. Similarly, ERP and MEG studies show reduced neural differentiation for consonant-vowel transitions [48] and attenuated vowel formant processing in the left auditory cortex linked to poor speech-in-noise performance [49], indicating that the grouping of acoustic elements into coherent percepts is compromised in ASD.

#### 1.2.2. Theoretical Frameworks: EPF, WCC and NCH

Three influential cognitive models, namely, Enhanced Perceptual Functioning (EPF), Weak Central Coherence (WCC), and the Neural Complexity Hypothesis (NCH), offer complementary explanations for these integration difficulties. These frameworks are particularly relevant when considering levels of complexity involving phonological features such as consonants (C) and vowels (V) as local, segmental units, and tone (T), as well as combinations like C + V, V + T, C + T, and C + V + T, as global, integrative features.

WCC posits a cognitive style in ASD that favors local detail processing at the expense of global integration [50]. Applied to speech, this suggests that children with ASD may process individual acoustic cues (e.g., formants) accurately but struggle to bind them into unified linguistic percepts. In contrast, EPF reframes this dissociation: rather than a deficit in global processing, it attributes the pattern to heightened sensitivity to local sensory inputs [51]. This can lead to “perceptual encapsulation,” where low-level features are processed in isolation, interfering with holistic integration. In line with WCC and EPF, individuals with ASD may demonstrate intact or heightened sensitivity to isolated, segmental features such as consonants or vowels while showing weakened neural responses to complex, multi-feature contrasts, including lexical tone or dual/triple feature combinations.

NCH further proposes that individuals with ASD may show intact or enhanced processing of simple stimuli, but progressively impaired responses as stimulus complexity increases [52]. Consistent with the NCH, meta-analytic findings show enhanced pitch discrimination in ASD, but also differences in how pitch is integrated into broader linguistic or musical contexts, suggesting a dissociation between basic auditory encoding and more complex integration processes [18].

The notion of stimulus complexity explains why even segmental features considered “local” like consonants may be more challenging than vowels: consonants require the integration of rapid, transient cues, placing higher demands on temporal parsing and neural synchrony. Indeed, neurophysiological data from non-autistic adults show that stop consonants evoke sparser cortical representations than vowels [53], suggesting they are not “simple” segmental features but rather inherently integrative. Thus, the distinction between “local” and “global” may be less about abstract feature type (e.g., C/V vs. T) and more about integrative cognitive demand. This reframing is critical: it suggests that problematic integration is not a single deficit, but a spectrum of processing burden that escalates with the number and complexity of interacting cues.

#### 1.2.3. The Developmental Imperative: Why Focus on Children?

Studying integration in school-age children (ages 5–10) is essential because this period represents a sensitive window for auditory and language development [54,55]. While foundational auditory plasticity, especially at the level of sensory encoding and language-specific speech representations emerges in infancy and is most pronounced during the first few years of life, higher-order auditory and language-relevant circuits retain plasticity well into childhood, extending through adolescence and adulthood [56,57]. This malleability allows us to capture core processing differences before compensatory strategies or environmental adaptations obscure them.

Moreover, mismatch negativity (MMN) paradigms that do not require focused attention to complete the task are particularly effective in this age group, showing high sensitivity to subtle group differences in auditory processing [20,34]. By focusing on this developmental stage, we can identify early neural markers of integration difficulties—markers that may predict later language outcomes and inform timely, targeted interventions. If integration deficits are rooted in developmental disruptions of neural synchrony or time-binding mechanisms [58,59], then childhood is the optimal window for detecting differences and implementing intervention. Understanding how EPF, WCC, and NCH manifest during this period will not only clarify the cognitive architecture of speech processing in ASD, but also guide the development of culturally and linguistically appropriate strategies to support speech perception and communication.

### 1.3. The Multi-Feature Oddball Paradigm

To investigate how children with ASD process and integrate multiple phonological features across varying levels of complexity, we employ a multi-feature oddball paradigm, an optimized and ecologically grounded variant of the traditional MMN design. Unlike standard paradigms that typically present a single deviant type amidst a high proportion of standard stimuli (80–90%), this approach introduces multiple types of deviants (e.g., tone, vowel, consonant) in an alternating sequence, with the standard stimulus presented only 50% of the time [60]. Each deviant differs from the standard in exactly one dimension, allowing for the efficient and simultaneous assessment of auditory discrimination across multiple speech features within a single, brief session. This design can reduce recording time to approximately 15–20 min while maintaining or even enhancing signal clarity [61].

The multi-feature oddball paradigm has been successfully adapted for speech stimuli by Pakarinen et al. (2009), who used consonant–vowel (CV) syllables as standards, with deviants involving changes in vowel, consonant, syllable pitch (F0), intensity, and duration [62]. This speech-specific version has been validated in both adults and children as young as 6 years old [63], demonstrating reliability and developmental appropriateness. Its ability to probe segmental (consonant/vowel) and suprasegmental (tone) processing within a unified framework makes it ideal for examining the interaction of multiple acoustic cues in a tonal language like Mandarin (See a recent study on Chinese adults [43]). For our purpose, the multi-feature paradigm is uniquely suited to test hierarchical integration. By embedding single-, dual-, and triple-feature deviants within the same experimental context, it allows us to systematically compare neural responses across increasing levels of integrative demand. This enables a direct test of our core hypotheses regarding local vs. global processing and the cumulative burden of feature complexity—questions that cannot be addressed using isolated, single-deviant paradigms.

Finally, the paradigm’s passive listening format minimizes cognitive and behavioral demands, making it highly appropriate for clinical and developmental populations [64,65,66]. It elicits robust ERP responses without requiring active participation, thereby capturing automatic auditory discrimination processes that are foundational to speech perception.

### 1.4. The Current Study

A key innovation of this study is the fine-grained analysis of auditory mismatch responses across varying levels of speech feature complexity. Unlike previous research, which has largely focused on isolated speech elements such as pitch, vowels, or consonants, and thus neglected their dynamic interplay, we aim to investigate how segmental (e.g., consonants, vowels) and suprasegmental (e.g., tone) features are processed and integrated in Mandarin-speaking children with ASD.

We employ a multi-feature oddball paradigm to examine whether children with ASD differ from typically developing (TD) peers in their sensitivity to single-, dual-, and triple-feature speech deviations. Neural responses will be assessed via the mismatch negativity (MMN), focusing on differences in amplitude, latency, and temporal coordination across processing stages. Although the P3a component is sometimes analyzed in the literature, its inconsistent reporting means it will not be a primary focus of our exploratory study.

Our study addresses four key questions:Do children with ASD show diminished MMN responses to speech feature deviations, with greater impairment for complex, multi-feature contrasts?Do ERP differences reflect processing delays that cascade across time, rather than isolated amplitude reductions?How do concurrent changes in tone, consonant, and vowel interact in ERP responses, and do children with ASD show atypical integration patterns in MMN?Given tone’s lexical role in Mandarin, do children with ASD show the most pronounced differences in tone-related conditions, suggesting a language-specific signature of speech processing difficulty?

To address these questions, we adopt a dual-framework approach that distinguishes between theory-driven and data-driven hypotheses. Our theoretical framework integrates three complementary models, WCC, EPF, and NCH, to explain auditory processing in ASD. Together, these models suggest a dissociation as our central hypothesis with specific prediction outlined in Table 1: enhanced or intact MMN responses to single-feature deviants (e.g., consonant or vowel changes), but attenuated or delayed responses to multi-feature deviants (e.g., C + V, V + T, C + V + T), reflecting impaired integration under increasing cognitive load. In this framework, consonants and vowels are tentatively classified as local, segmental features, while tone and multi-feature combinations are treated as global, integrative features.

However, we acknowledge that this local/global conceptual distinction may not fully reflect the neurophysiological reality or complexity of speech perception and thus may not represent the EPF/WCC models accurately. As mentioned earlier, consonant and vowel perception is not purely based on “local” or “isolated” segmental features in the abstract sense as they may involve integration of multiple acoustic cues (e.g., VOT, formant transitions), which can place significant demands on global processing mechanisms. Given the exploratory nature of this study, we treat this framework as provisional—a hypothesis-generating lens to be validated against empirical data.

In contrast to the theory-driven approach, Table 2 specifies predictions based on empirical findings from the MMN literature, focusing on how each stimulus condition may behave in ASD, regardless of theoretical assumptions. When additional features are involved for more complex processing, presumably the MMN differences in amplitude and latency will be magnified in the tired system going from single- to dual- to triple- feature contrasts due to integration difficulties in ASD reported in the literature. While the overall data-driven hypothesis from the MMN literature is that children with ASD will show reduced MMN amplitudes and prolonged latencies across all speech stimulus conditions with effects worsening with complexity, vowel processing stands as a notable exception. As reviewed earlier, some studies have found that children with ASD exhibit prolonged MMN latencies (but not reduced MMN) for vowel stimuli and reduced P3a responses, indicating delayed sensory encoding and impaired attentional orienting to vowel changes. Especially when considering individual variability in language ability or sensory preferences, intact MMN responses may also occur for various speech contrasts (including consonants and vowels) in some subgroups of ASD populations. It is also worth noting that not all MMN studies explicitly report hemispheric data for MMN analyses. Given the growing body of evidence indicates atypical hemispheric specialization for speech in ASD, we tentatively hypothesize that this reduced left-hemispheric MMN advantage (which is not specified in WCC/EPF/NCH models) will be evident across all stimulus conditions, particularly for complex, linguistically relevant contrasts.

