#### 3.1.1. t-PCA-Level Predictions (P)

P1 (Component Variance): The proportion of variance explained by temporally decomposed MMN components (eMMN, lMMN) will be lower in the ASD group for multi-feature deviants (V + T, C + T, C + V + T), reflecting less structured neural responses under high integrative demand.

P2 (Factor Scores): Factor scores for MMN-related components will be significantly reduced in the ASD group, particularly for tone-involving conditions (T, V + T, C + T, C + V + T), consistent with a global integration deficit.

P3 (Temporal Dynamics): The ASD group will show a delayed peak in late MMN (lMMN) components across all conditions, with the greatest delay observed for triple-feature deviants, supporting NCH’s prediction of cascading processing delays.

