#### 3.2.1. t-PCA-Level Predictions

P7 (Amplitude Attenuation): Across all conditions (with the exception of vowel deviation), the ASD group will show lower factor scores for MMN components, with the most severe reductions in multi-feature conditions.

P8 (Latency Prolongation): Peak latencies of eMMN and lMMN components will be systematically delayed in the ASD group, with delays increasing as feature complexity rises.

P9 (Component Blurring): The temporal separation between eMMN and lMMN components will be less distinct in the ASD group, suggesting a breakdown in the normal cascade of auditory processing stages.

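### P3 reads a delayed late-MMN peak as support for cascading delays, but neither P3 nor P8 compares the late delay with the early one

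*Protocol article*

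**What the plan says.** Section 1.4 poses key question 2, "Do ERP differences reflect processing delays that cascade across time, rather than isolated amplitude reductions", and names no measure for it.

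The measure appears in section 3.1.1. P3 states: "The ASD group will show a delayed peak in late MMN (lMMN) components across all conditions, with the greatest delay observed for triple-feature deviants". It offers this as support for NCH's "prediction of cascading processing delays". P3 concerns lMMN only.

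Section 3.2.1 has two further timing predictions. P8 reads: "Peak latencies of eMMN and lMMN components will be systematically delayed in the ASD group, with delays increasing as feature complexity rises". P9 reads: "The temporal separation between eMMN and lMMN components will be less distinct in the ASD group, suggesting a breakdown in the normal cascade".

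The end of section 3.2.2 disclaims strong advance predictions about the separate roles of early and late MMN, and labels findings on MMN timing as post hoc and exploratory. Section 2.3.3 runs one t-PCA over all participants and conditions, places eMMN at about 100–200 ms and lMMN at about 200–300 ms, and takes mean amplitudes from the reconstructed components. Section 3 says latency is also derived from the components but does not say how.

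**The concern.** A claim that delays cascade over time is a claim about how the late stage relates to the early stage. P3 looks at the late stage alone. P8 looks at both stages but grades the delay by number of features, not from early to late. Neither asks whether the lMMN delay exceeds the eMMN delay.

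The article itself supplies a rival explanation. Section 1.1.2 says: "Children with ASD show longer latencies in auditory evoked responses, reduced neural synchrony and lower MMNs". A delay already present in the early response and carried forward unchanged would make lMMN late as well. If P3 is met, the study could answer the cascade part of key question 2 positively on data that show a delay of the same size at both stages.

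**Working it through.** **Inputs from the article.** 30 children per group (section 2.1.2); seven deviants, of which three change one feature, three change two and one changes three (Table 3); P3, P8 and P9 as quoted. **Assumed, because the article gives no figure:** the latency SD, the eMMN–lMMN latency correlation and the size of the delays.

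**Step 1: the logic.** Let dE and dL be the ASD-minus-TD delay of the eMMN and lMMN peaks. The group difference in the within-child interval is dL − dE. It is above zero when the delay grows, zero when both peaks shift equally, and below zero when the interval shortens.

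Take delays of 10, 20 and 30 ms for one, two and three features, the same in both components:

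| Features | dE | dL | dL − dE |
|---|---|---|---|
| 1 | 10 | 10 | 0 |
| 2 | 20 | 20 | 0 |
| 3 | 30 | 30 | 0 |

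lMMN is late in every condition and latest for the triple deviant, so P3 is met. Both components are late and the delay rises with complexity, so P8 is met. The interval does not change.

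**Step 2: simulation with one delay per component.** Bivariate normal latencies, correlation 0.5, two-sided 5% t-tests, 10,000 runs. Entries are for SD 15 / 25 / 35 ms.

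| Early, late delay (ms) | lMMN significantly later | Interval significantly longer |
|---|---|---|
| 20, 20 (equal shift) | 99.9 / 86.0 / 59.0% | 2.4 / 2.5 / 2.3% |
| 10, 30 (growing) | 100 / 99.6 / 90.6% | 99.9 / 86.4 / 59.3% |
| 0, 20 (late only) | 99.9 / 85.6 / 57.7% | 99.9 / 86.1 / 58.2% |

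A significant lMMN delay is common in all three rows, so it cannot tell them apart. The interval separates the first row from the other two. The 2.3–2.5% is one tail of a 5% test when the true difference is zero, so it is expected by construction.

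**Step 3: simulation with the graded delays of Step 1.** Seven conditions, child SD 20 ms per component, correlation 0.5, condition noise SD 25 ms, 8,000 runs. The lMMN delay averaged over conditions is significant in 84%, the triple deviant shows the largest observed delay in 71%, and both hold in 59%. If the second clause must instead be a significant contrast of the triple deviant with the mean of the other six, both hold in 47%. The interval is significantly longer in about 3%, which is close to chance.

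**Step 4: what the interval contrast can detect.** Smallest gap at 80% power = (1.96 + 0.84) × √(2(1 − r)) × √(2/30) latency SDs.
- r = 0.5: 2.80 × 1.00 × 0.258 = 0.72 SD, or about 11, 18 and 25 ms at SD 15, 25 and 35 ms.
- r = 0.3: 0.86 SD.
- r = 0.7: 0.56 SD.

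**Step 5: where latency can come from.** A back-projected component is a fixed temporal loading multiplied by a score. The score changes height and sign, not the time of the peak. A loading peaking at 248 ms, multiplied by three different scores, peaked at 248 ms each time. With one pooled t-PCA, the peak time is therefore the same for every child and condition.

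**Step 6: P9.** If its temporal separation means the interval between peaks, P9 implies dL < dE, the opposite sign to a growing delay. If it means overlap of the components, as its label about blurring allows, it says nothing about the sign of dL − dE.

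**The case against.** - **The question itself draws no such inference.** Key question 2 contrasts delay with amplitude loss and names no measure. This stands: the inference is made in P3, and P3 is what needs changing.
- **The article does not define a cascade as a growing delay.** An early delay passed on to the next stage is also an ordinary meaning, and P8 bears on it. This stands in part. P3, however, does not include eMMN, so it cannot show inheritance either.
- **P3 is not met by slowing that is the same in all conditions.** A reader might infer that any general slowing would pass as a cascade with no integration content. The article does not support that. P3 also requires "with the greatest delay observed for triple-feature deviants", which is real evidence on complexity and so on NCH. Uniform slowing would also conflict with Table 1, which predicts equal or shorter latency for consonant-only and vowel-only deviants. What passes P3 is a delay equal across stages and graded by feature number.
- **P9 need not contradict P3 or P8.** A reader might infer that P9 predicts the opposite of a growing delay. That needs the interval reading, which the text leaves open. P9 and P3 also belong to two prediction sets offered as competing accounts, so a difference between them is not in itself an error.
- **Timing results are labelled exploratory.** This is true and lowers the stakes, but the label does not make an lMMN delay able to distinguish growth from an equal shift. P3 still attaches the cascade interpretation to it.

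**Conclusion.** The concern holds as a point about P3 and its link to key question 2. An lMMN delay that is greatest for triple deviants supports delay and dependence on complexity. It does not show that delay grows from the early to the late stage, and P8 does not fill the gap. The logic of Step 1 needs no assumed figure. The percentages do: latency SDs, correlation and delay sizes are all assumptions, and the late-delay rate under an equal 20 ms shift moves from 99.9% to 59% across the SDs tried. The change is worth making before analysis. It does not undermine the design, and no result has yet been misreported.

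**What to change.** - Make the ASD-TD difference in the within-child interval (lMMN minus eMMN latency), and its change with feature number, the measure for the cascade part of key question 2, with confidence intervals. Report the eMMN delay beside it, because a late-only delay also lengthens the interval.
- Take latencies from a signal in which they can differ between children, such as each child's own difference waves.
- Report the latency of the response to the standard /ba1/ (980 presentations, section 2.2.2) as a reference for general slowing.
- Reword P3 so that an lMMN delay alone supports delay and complexity-dependence. Reserve the cascade wording for a longer interval in ASD. Report an inconclusive interval as inconclusive, not as general slowing.
- State whether P9 means peak interval or component overlap.

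**Cost.** No new data are needed: the work is added latency measurement, one further contrast with its trend over feature number, and rewording. A cascade claim becomes harder to make. Peak latencies from individual waveforms are noisier and less well separated than t-PCA components, which matters because the two windows adjoin. With 30 per group the contrast has 80% power only for gaps of about 0.72 latency SD or more (assumed correlation 0.5).
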